### 3.2 Indication: port-wine stains

### 3.3 Randomization

In this randomized and double-blinded trial, each subject should be assigned a drug serial number strictly in accordance with the inclusion time sequence to determine the treatment group. Stratified block randomization was performed; and a software analysis system is used to generate continuous serial numbers corresponding to the sample size. The randomization numbers for each study center are generated at the same time. The sealed randomization table is maintained by the leading

institution and sponsor separately.

3.4 Trial plan: this clinical study is scheduled to complete between September 2008 and December 2009.

### 3.5 Subject selection

#### 3.5.1 Inclusion criteria

All the patients participating in this clinical study must satisfy all the following criteria:

- The patients must be clinically diagnosed as port-wine stains;
- Male or female patients aged 14~65 years;
- The patients have read the subject's instructions and are willing to receive the treatment per protocol requirements and complete the visits in timely manner;
- The patients agree to sign the written informed consent form (ICF);
  - ✧ For subjects aged <18 years, both the subjects and legal guardians should sign the ICF at the same time.

#### 3.5.2 Exclusion criteria

The patients who meet any one of the following criteria must be excluded from this clinical study:

- The affected area has other concomitant skin diseases (e.g. severe acne, contact dermatitis, or purulent infection) that may affect the efficacy evaluation;
- The treatment area has been treated with isotope therapy, PDT or other therapies that may affect the efficacy evaluation;
- The patients are currently suffering from allergic diseases; the patients have known photosensitive dermatitis and porphyria or known history of allergies to the trial drug (porphyrins) and drugs with similar chemical structure;
- The patients have allergic constitutions, scarring constitutions or scarring tendency;
- The patients used known photosensitive drugs such as griseofulvin, thiazide diuretics, sulfonylureas, phenothiazines, sulfonamides, retinoic acids, quinolones and tetracyclines within 1 month
- The patients have known severe immunocompromised conditions or require long-term use of corticosteroids and immunosuppressants;
- The patients have ECG abnormalities and organic heart diseases;

- Abnormal liver function (ALT and AST exceed the upper limit of normal (ULN), TBIL exceeds 1.5xULN) or severe renal dysfunction (renal function index exceeds 1.5xULN);
- The patients have hereditary or acquired coagulation disorders or are using anticoagulants;
- The patients have severe neurological, mental and endocrine disorders;
- The patients received systemic therapies to treat port-wine stains within 4 weeks prior to this treatment;
- The patients received topical therapies to treat port-wine stains within 2 weeks prior to this treatment;
- Pregnant and lactating women or women using inappropriate contraceptive measures;
- The patients participated in other drug clinical trials within 4 weeks prior to this treatment.

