The mechanism of PDT for the treatment of port-wine stains: because the photosensitizer obtains a plasma concentration peak immediately after its intravenous injection followed by rapid absorption by the vascular endothelial cells with little absorption in the epidermal cells, the distribution of injected photosensitizer forms an apparent concentration gradient between the vascular endothelial cells and the epidermal cells. Then transepidermal laser irradiation using specific wavelengths of selective absorption can activate the photosensitizers to generate singlet oxygen and other phototoxic substances, leading to selective destruction of the dilated and malformed capillary networks containing abundant photosensitizers at the lesion site without damaging the top normal epidermis containing little photosensitizers, the underneath dermal tissues are also protected because the limited laser penetration.

Photosensitizer is one of the key factors of PDT efficacy. Despite the significant results achieved with clinical application of the first generation of photosensitizers (hematoporphyrin derivatives, HpD), the skin phototoxicity reaction still lasts for 1~2 months and up to 3~4 months in some patients because HpD is a mixture of multiple porphyrins with strong affinity with collagen fibers,

its composition and chemical structure are yet to be clarified fully, and its excretion from the body is fairly slow. The patients must be strictly protected from light during this period, which severely affect not only the patient's quality of life and work but also cause great inconvenience in clinical treatment. Therefore, the current issue to be addressed urgently in order to meet the clinical demands on PDT is to develop photosensitizers with single chemical composition, clear structure, stable physicochemical properties, ideal action spectrum, high target tissue selectivity, strong photodynamic effect, low toxicity, and rapid metabolism.

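### The exclusion criteria can admit patients who, by the protocol's own figures, are still phototoxic from an earlier systemic photosensitiser given for another area

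*Protocol*

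**What the plan says.** Section 1 (Trial background) describes the first-generation photosensitiser HpD: "the skin phototoxicity reaction still lasts for 1~2 months and up to 3~4 months in some patients". It explains this by tissue binding, "because HpD is a mixture of multiple porphyrins with strong affinity with collagen fibers", and by slow excretion, and adds that patients have to stay strictly out of the light for that time.

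Section 3.5.2 (Exclusion criteria) deals with earlier treatment in four places:

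- Earlier PDT, with no time limit but tied to the area: "The treatment area has been treated with isotope therapy, PDT or other therapies that may affect the efficacy evaluation".
- Systemic port-wine stain therapy: "The patients received systemic therapies to treat port-wine stains within 4 weeks prior to this treatment".
- Photosensitising drugs: "The patients used known photosensitive drugs such as griseofulvin, thiazide diuretics, sulfonylureas, phenothiazines, sulfonamides, retinoic acids, quinolones and tetracyclines within 1 month". The examples include no porphyrin photosensitiser.
- Other drug trials, within 4 weeks.

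Section 4.3 has the target lesions irradiated at 532 nm and 80-100 mW/cm² for 20 minutes, with no exemption for the placebo group. Under section 3.1 the control group receives placebo in course 1 and hemoporphin in course 2. Section 2 includes both stages in the safety analysis.

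**The concern.** The earlier photosensitiser acts on the whole patient, but the PDT exclusion looks only at one area of skin. The criteria that do apply to the whole patient have windows at or below the low end of the persistence that the protocol reports for HpD. Someone who had HpD-PDT on the neck six weeks ago and now presents a facial lesion passes every criterion, although section 1 implies that this person may still need strict light protection.

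Two things follow. Such a patient, in either group, would be put under the laser while possibly phototoxic. And a phototoxic reaction in that patient may be attributed to hemoporphin: section 4.3 lists photosensitive reactions among the adverse reactions to expect, and the causality categories in section 9.2.2 do not mention an earlier photosensitiser. Rapid clearance and a short period of light protection are part of the case that section 1 makes for the drug, so carry-over from HpD would blur the property of interest.

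**Working it through.** **Inputs.** HpD phototoxicity lasts 1-2 months, and up to 3-4 months in some patients (section 1). The windows are 4 weeks = 28 days and 1 month (section 3.5.2). Course 1 lasts 8 weeks = 56 days (section 3.1). I count a month as 30 days, so persistence is 30-60 days in the usual range and 90-120 days in the tail.

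**Step 1: the gap.** Gap = persistence minus window.

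| Persistence (days) | Minus 28 | Minus 30 |
|---|---|---|
| 30 | 2 | 0 |
| 60 | 32 | 30 |
| 90 | 62 | 60 |
| 120 | 92 | 90 |

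The gap is 0 to 32 days in the usual range and 60 to 92 days in the tail. The 30-day column also covers the reading in which HpD is counted among the photosensitising drugs, so that reading does not close the gap.

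**Step 2: how far it reaches into the trial.** Take a patient entered 31 days after HpD.

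- Usual range: at 60 days' persistence, 60 - 31 = 29 days of course 1 are affected, and the effect is over before course 2.
- Tail: 90 - 31 = 59 and 120 - 31 = 89 days remain, more than the 56 days of course 1. Course 2 would start at day 31 + 56 = 87, inside the tail by 3 to 33 days.
- Residual phototoxicity at the start of course 2 therefore needs tail persistence and entry within 90 - 56 = 34 to 120 - 56 = 64 days of the HpD dose.

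**Step 3: does it matter for the primary test?** First the plan's own sample size. Section 3.1 assumes 75% response on hemoporphin and a 40-point difference, hence 35% on placebo, with two-sided α = 0.05, 90% power and 3:1 allocation. With p̄ = (0.75 + 0.35)/2 = 0.55,

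n(control) = (1.960 + 1.282)² × 0.55 × 0.45 × (1 + 1/3) / 0.40² = 21.7,

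which rounds up to 22 controls and 66 trial subjects. The stated figures are reproduced.

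Now suppose that a share f of placebo subjects responded like treated subjects. The documents give no value for f, so this is an assumption chosen to be unfavourable. Placebo response = 0.35 + 0.40 f, and power is at the planned 330/110:

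| f | Placebo response | Difference | Power |
|---|---|---|---|
| 2% | 35.8% | 39.2 points | above 99.99% |
| 5% | 37.0% | 38.0 points | above 99.99% |
| 10% | 39.0% | 36.0 points | above 99.99% |
| 20% | 43.0% | 32.0 points | above 99.99% |
| 50% | 55.0% | 20.0 points | 97.2% |

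Even implausibly heavy contamination leaves the test well powered, and it would shrink the difference, which works against hemoporphin.

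**The case against.** A reader might infer that a placebo subject with residual HpD would receive effective PDT, so that the control is no control. The documents do not support that. Section 1 ties lesion clearance to the first minutes after dosing: "the photosensitizer obtains a plasma concentration peak immediately after its intravenous injection followed by rapid absorption by the vascular endothelial cells". It ties HpD's persistence to collagen. Lingering skin phototoxicity is not the same as selective vascular effect weeks later, and nothing says that the latter occurs. Step 3 shows that it would matter little to the test if it did.

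Other objections also carry weight:

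- The PDT criterion is not a short washout. It bars any earlier PDT of the treatment area, so the gap concerns other areas only.
- A reader might extend the gap to PDT for other diseases. Section 1 names such uses but does not say that they involve HpD or any systemic porphyrin, and the persistence figure is given for HpD alone.
- Randomisation spreads such patients over both groups in expectation, which protects the course-1 comparison of adverse events. The causality categories allow for other causes, and earlier treatment is on record. Misattribution is a risk in single cases, not a certainty.
- Persistence through all of course 1 needs the tail, which section 1 limits to some patients.
- Hemoporphin's own light-protection period is 2 weeks (section 4.3), so a 4-week window covers earlier hemoporphin.

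These points narrow the consequences but do not close the gap. The exclusion of known photosensitive dermatitis does not close it either, because a patient who has kept out of the light need not have had any dermatitis. Section 4.8 restricts drugs only during the trial.

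**Conclusion.** The point stands as an internal mismatch between the background and the exclusion criteria. By the protocol's own figures, a patient treated with HpD on another area can enter while still phototoxic, with an uncovered gap of about 0 to 32 days in the usual range and 60 to 92 days in the tail. The consequences are safety at the laser session, in both groups and both courses, and case-level attribution of phototoxic reactions. Attribution is weakest in course 2, where everyone receives hemoporphin, although by then only tail cases remain.

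It should not be read as a threat to the primary result or as evidence that placebo subjects receive working PDT. The conclusion assumes 30-day months and that some candidates have had HpD recently. The protocol gives no number for these, and they may be few.

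**What to change.** Reconcile section 1 with section 3.5.2. Let the exclusion for an earlier systemic photosensitiser apply to the whole patient and not only to the treatment area, and have the sponsor set its window and justify it against the persistence stated in section 1. The length is a clinical decision for the sponsor. The criterion should also say whether porphyrin photosensitisers fall under the photosensitising-drug rule, whose examples leave this open.

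No new procedure is needed: section 7.1 already records earlier treatment at enrolment, and the section 6 flowchart places history and therapies on Day 1. The cost is one amended criterion and a few candidates with recent PDT elsewhere who are deferred or lost. With 330/110 planned against a calculated minimum of 66/22, the primary test can bear a small loss, but candidates who are lost would have to be replaced to keep the trial group at the regulatory minimum of 300.

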#### 4. Trial materials and methods

4.1 Trial drug: hemoporphin lyophilized powder for injection, 100mg/vial, is manufactured by Shanghai Fudan-Zhangjiang Bio-Pharmaceutical Co., Ltd. There are totally 2 batches of trial drugs, the first batch number is 080601, manufacture date: June 2008, date of expiry: May 2010; the second batch number is 081201, manufacture date: Dec. 2008, date of expiry: Nov. 2010.

4.2. Trial light source: laser apparatus with a wavelength of 532nm, continuous or quasi-continuous output and maximum output power of no less than 5W.

#### 4.3 Treatment methods

- 1) Hemoporphin solution is prepared per the trial dose. The prepared drug solution is a dark red transparent liquid and should be inspected for precipitation or discoloration phenomenon prior to injection.
- 2) The injection site skin is sterilized routinely.
- 3) Intravenous infusion of the drug solution should be at a constant speed using an infusion pump, and be completed within 20min. The relatively large veins easily protected from exposure to light should be selected (the largest vein in the arm such as the median cubital vein is preferred and small veins in the back of the hand should be avoided); 1ml physiological saline is injected for confirmation prior to drug infusion to prevent drug leakage into the extravascular space. Additional 2~4ml physiological saline should be infused at ending of drug infusion to decrease the intravascular drug concentration in order to prevent

photosensitive reactions at the injection site. The photosensitizers should be protected from light during the preparation and injection process to avoid efficacy decline. Measures should be taken to protect the subjects from light after drug infusion.

- 4) The target lesions are irradiated with 532nm laser and irradiation power density of 80-100 mW/cm^2.

☞ Irradiation time: the laser irradiation begins 10min after beginning of drug infusion and ends 20min later. The total irradiation time is 20 minutes.

☞ Precautions during laser irradiation: ① depending on the lesion size and site, the selected treatment areas should be as flat as possible; the hair-covered areas (eyebrow, beard and hairline) need to be shaved clean to avoid affecting laser irradiation. The non-treatment area surrounding the lesion, especially the nasolabial fold and other weak areas should be carefully covered with adhesive tapes and double-layer red-black clothing; ② the output power at the fiber terminal should be adjusted and measured according to the therapeutic regimen prior to irradiation, the beam expander should be maintained perpendicular to the irradiation surface; in addition, it is necessary to pay attention to the size of the beam spot, closely observe the changes in the irradiated areas, and accurately control the irradiation time; ③ the output power need to be monitored before, after and during the irradiation process.

- 5) Precautions: the patients should be instructed to observe the photoreaction after drug infusion and pay attention to photo protection. The photoreaction is expected to disappear completely in approximately 10 days after drug infusion. During the light protection period (2 weeks), the subjects should pay attention to protection of the exposed skin and eyes, avoid irradiation of sunlight or strong indoor lights. In case of drug extravasation during the infusion, the extravasation area must be kept completely away from light for a fairly long time until local swelling and discoloration disappears completely, otherwise severe local skin photoinjury may occur.
- 6) PDT may cause the following treatment reactions: the patients may experience itching, burning sensation, pain, swelling, blisters and scabs at the irradiated and surrounding area. These therapeutic responses are usually transient and self-healing without special treatment.
- 7) Adverse reactions: If light protection measures are not taken properly, some patients may experience photosensitive reactions such as photosensitive dermatitis, photosensitive ophthalmia, photosensitive cheilitis, etc; some patients may experience nausea, dizziness, headache, drowsiness, total bilirubin elevation, hyperpigmentation, hypopigmentation,

treatment site infection, scarring and other adverse reactions.

- 8) At week 8 after the first treatment, if the color of treatment area has not subsided completely and there are no serious pigmentation, scarring and other conditions that are unsuitable for re-treatment according to the investigator's judgment, the next stage treatment can be carried out.

#### 4.4 Drug packaging and blinding

Because the drug used in this trial is powder for injection and the doses for the control group and trial group are different, stimulant is inappropriate for the double-blinded design; considering the fact that the trial drugs are prepared by nurses, the sponsor will prepare the drugs for each group per the double-blinded requirement during the drug preparation period.

Identical drug outer packaging are used for both groups; each patient needs an independent large packaging that contains two medium packaging marked with "drugs for the first course of treatment or drugs for the second course of treatment". Each medium packaging includes drugs for trial group (5 bottles of drugs in each medium packaging) and control group (each medium packaging contains 5 empty bottles for the first course of treatment and 5 bottles of drugs for the second course of treatment).

The statisticians will provide the random number table generated using DAS software simulation and provide it for random blinding of the drugs. Stratified block randomization is carried out by trial centers. Drug coding is completed by personnel unrelated to this clinical trial.

During the trial period, each center assigns a special person to manage the trial drugs and a nurses will prepare the trial drugs, keeping the investigators and subjects blinded.

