## 3. Trial design

### 3.1 Design principle:

This is a parallel, placebo-controlled, double-blinded and multicenter clinical trial.

The subjects are randomized into trial group and control group at 3:1 ratio in this phase III clinical trial.

Statistical estimation of the sample size: using two-sided test of the efficacy,  $\alpha=0.05$  and  $\beta=0.1$  (power=90%) based on phase II clinical trial results, the expert panel estimates the total clinical efficacy rate of hemoporphin for injection to be 75.0% in the treatment of port-wine stains and expects a 40% difference from the placebo group; consequently, the estimated minimal number of subjects is 66 for the trial group and 22 for the control group.

In compliance with the SFDA requirement of minimum sample size of no less than 300 subjects for phase III clinical trial group, and also taking into account of dropout, the sample size of this clinical trial was determined to be 330 subjects for the trial group and 110 subjects for the control group, giving a total of 440 subjects.

The subjects will be assigned into trial group or control group by stratified block randomization to receive not more than 2 courses of treatment. The control group receive placebo during the first course of treatment followed by trial drug during the second course of treatment. Each course of treatment will last for 8 weeks. Based on the phase II clinical trial results, the trial drug dose is set at 5mg/kg.

The trial design profile is shown in the following table.

| Trial period                   | Hemoporphin for injection dose | Group and number of cases     | Design principle                                                          |
|--------------------------------|--------------------------------|-------------------------------|---------------------------------------------------------------------------|
| The first course of treatment  | 5mg/kg                         | 330 subjects in trial group   | Randomized, double-blinded, placebo and parallel-controlled (multicenter) |
|                                | 0mg/kg                         | 110 subjects in control group |                                                                           |
| The Second course of treatment | 5mg/kg                         | 330 subjects in trial group   | Randomized, double-blinded (multicenter)                                  |

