#### 4.5 Trial drug distribution and dispensing

Both the trial drug and light source are provided by Shanghai Fudan-Zhangjiang Bio-Pharmaceutical Co., Ltd. and delivered to all study centers periodically per the protocol by the company's clinical study monitors. The drugs are distributed by a special person at each study center. The observation doctors should dispense the drugs by the order of each patient's visit and the sequence of drug numbers without choosing the drugs intentionally. The drug numbers remain unchanged throughout the trial process. After successful enrollment, the patients will be offered with sufficient dose of trial drug of identical labels.

The drug managers should fill out the drug dispensing/recovery registration form timely and accurately.

An emergency letter should accompany each of the trial drugs and the letters will be maintained by the principal investigator of the participating institution.

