#### 5. The total number of subjects, grouping, randomization method and the tasks undertaken by each center

The total number of subjects planned to include is 440 and the distribution of these subjects among the centers are listed in the following table:

| Centre No. / Clinical study institution                                                    | Trail group | Control group | Total |
|--------------------------------------------------------------------------------------------|-------------|---------------|-------|
| 1. Peking University First Hospital                                                        | 39          | 13            | 52    |
| 2. Institute of Dermatology, Chinese Academy of Medical Sciences                           | 39          | 13            | 52    |
| 3. The Ninth People's Hospital of Shanghai Jiaotong University School of Medicine          | 57          | 19            | 76    |
| 4. Guangzhou General Hospital of Guangzhou Military Region                                 | 39          | 13            | 52    |
| 5. Huashan Hospital of Fudan University                                                    | 39          | 13            | 52    |
| 6. Xijing Hospital of the Fourth Military Medical University                               | 39          | 13            | 52    |
| 7. Union Hospital of Tongji Medical College, Huazhong University of Science and Technology | 39          | 13            | 52    |
| 8. Xiangya Hospital of Central South University                                            | 39          | 13            | 52    |
| Total                                                                                      | 330         | 110           | 440   |

The number of subjects can be adjusted according to the inclusion rate at each center.

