### 9.3.3 Opening the emergency letters and unblinding:

Blinding should be well kept throughout the study. However, in case of emergency and when it becomes really necessary to identify the type of drug a patient has received, the principal investigator of the study institution can open the emergency letter (in each set of drugs) which contains the drug name and number for this patient. The monitors should be notified of the process immediately. The investigators should record in CRF the reason and date of unblinding in detail and sign on the record. Once unblinded, the patient will have to be discontinued in this trial and treated as a dropout case.

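### Concealment of the next allocation is weakly protected: the printed centre quotas suggest a fixed 3:1 block of 4, kit contents reveal the arm at the site, and codes for unused numbers are kept there.

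*Protocol*

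**What the plan says.** Section 3.1 sets the ratio: "The subjects are randomized into trial group and control group at 3:1 ratio in this phase III clinical trial". Section 4.4 adds: "Stratified block randomization is carried out by trial centers". No block size is given.

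Numbers are used in order. Section 3.3 states that "each subject should be assigned a drug serial number strictly in accordance with the inclusion time sequence", and section 4.5 that "The observation doctors should dispense the drugs by the order of each patient's visit and the sequence of drug numbers".

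The table in section 5 gives every centre's planned number by arm: 39 trial and 13 control at seven centres, 57 and 19 at the eighth, 330 and 110 in all. It then adds: "The number of subjects can be adjusted according to the inclusion rate at each center".

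Under section 4.4 the outer packaging is identical. For the first course, however, the trial kit holds five bottles of drug and the control kit five empty ones. A nurse at the centre prepares the dose, and the blinding claim covers investigators and subjects. Section 4.3 describes the prepared drug as a dark red liquid and lists local reactions that treatment may cause. Section 4.6 has investigators record the bottles used.

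On the emergency codes, section 4.5 says each drug has a letter and "the letters will be maintained by the principal investigator of the participating institution". Section 9.3.3 says "the principal investigator of the study institution can open the emergency letter (in each set of drugs", which places the letter in the kit.

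**The concern.** This point is about concealment before enrolment. Blinding of the efficacy assessment after treatment is a separate matter.

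Small blocks within a centre are safe only while past allocations in the current block stay hidden. Here the per-arm quotas invite a reader to infer the block size. At least one person at each site learns every first-course arm on opening the kit. Doctors who enrol also handle kits and bottle records and see patients afterwards. The codes for numbers not yet used are at the enrolling site under either description of the letters.

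A doctor who can infer the next arm can delay or select patients by expected response. There is room for this: consent, eligibility, lesion typing and number allocation all fall on Day 1 in the section 6 flowchart, and some exclusions in section 3.5.2 turn on judgement. Such selection would enter the response-rate difference directly, and a larger sample would not reduce it.

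**Working it through.** **Inputs.** Ratio 3:1 (section 3.1); quotas 39:13 and 57:19 (section 5); planned response 75% against 35%, that is 75% less the expected 40 points (section 3.1); 330 and 110 subjects.

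**Quotas reproduced.** 7 × 39 + 57 = 330 and 7 × 13 + 19 = 110, total 440. Each centre is exactly 3:1.

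**Which block sizes fit.** A 3:1 block must be a multiple of 4.
- Constant size: 52 = 4 × 13 and 76 = 4 × 19, with 13 and 19 prime. The multiples of 4 that divide 52 are 4 and 52; those that divide 76 are 4 and 76. The only constant size below a whole centre is therefore 4.
- Mixed sizes: 52 = 1 × 4 + 6 × 8 and 76 = 1 × 4 + 9 × 8. Also 52 = 2 × 8 + 3 × 12 and 76 = 2 × 8 + 5 × 12. These fill the same quotas.

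**Predictability with a fixed block of 4.** Suppose all earlier allocations in the block are known.

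| Position of the control | Certain trial slots | Certain control slots | Total |
|---|---|---|---|
| 1 | 3 | 0 | 3 |
| 2 | 2 | 0 | 2 |
| 3 | 1 | 0 | 1 |
| 4 | 0 | 1 | 1 |

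The mean is 7/4 = 1.75 of 4 slots, or 43.75%. Over the trial, 0.4375 × 440 = 192.5. By arm this is 6 of 12 trial slots (50%, or 165 of 330) and 1 of 4 control slots (25%, or 27.5 of 110).

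**Other designs, same observer.** A fixed block of 8 (6:2) gives 28.6% by enumeration, and a fixed block of 12 (9:3) gives 21.3%. Randomly mixed blocks of 4 and 8, equally likely, were simulated with an observer who knows both sizes and every past allocation but not the order of sizes. The share certain is 10.5% for a centre of 52 and 10.7% for a centre of 76, so about 10%.

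**What it could do to the estimate.** Assume that in every certain slot the expected response is shifted by d points in the direction that favours the drug. The trial arm rises by 0.5d and the control arm falls by 0.25d, so the bias in the difference is 0.75d.
- d = 5: 3.75 points
- d = 10: 7.5 points
- d = 20: 15 points

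For scale, the 95% half-width at the planned rates is 1.96 × √(0.75 × 0.25/330 + 0.35 × 0.65/110) = 0.101, or about 10 points. The protocol gives no value for d; the range is an assumption.

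**The case against.** A reader might infer that the quotas prove a fixed block of 4. They do not. Mixed blocks of 4 and 8, the remedy itself, can produce exactly these numbers, a last block may be left incomplete, and section 5 allows the numbers to be adjusted. The size may rightly be kept in a restricted document. This part of the objection stands.

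A reader might also infer that enrolling doctors know each past allocation. The text shows this only for whoever opens the kit. Section 4.4 separates a drug manager and a preparing nurse from the blinded investigators, and section 4.3 says only that reactions may occur. The doctors' knowledge is an inference from their contact with kits, bottle records and patients. That stands too, but no sentence bars staff who have seen the contents from taking part in enrolment.

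Holding the letters is not the same as reading them. Section 9.3.3 limits opening to emergencies, requires the monitors to be told and the reason to be recorded and signed, and removes the patient from the trial. These rules deter misuse. They do not separate custody from enrolment, and sections 4.5 and 9.3.3 still differ on where the letters are kept.

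Other safeguards exist. The randomisation table is sealed, coding is done by people outside the trial, section 4.5 forbids deliberate choice of kits and supplies drug after enrolment, and the flowchart lists eligibility ahead of number allocation. Controls receive active drug in the second course, which weakens the motive to steer. Sections 14.2.2 and 14.5 allow adjustment for centre, lesion type and unbalanced baseline factors. That would remove part of a selection effect, but only the part carried by recorded factors that are put in the model.

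**Conclusion.** The point holds as an avoidable weakness in concealment. The documents do not show that a leak has occurred or that the block size is 4.

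The figure of 43.75% (about 193 of 440) is an upper bound. It needs blocks fixed at 4 and complete knowledge of past allocations. The bias of 0.75d needs, in addition, that every certain slot is exploited at every centre. Undisclosed blocks of 4 and 8 would bring the certain share down to about 10% even for a fully informed observer.

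The protocol's own text creates the exposure: exact per-arm quotas, kits whose contents show the arm, and unused codes at the site. Since the remedy costs almost nothing, the change should be made.

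**What to change.** - Sections 3.3 and 4.4: state that block sizes vary at random within each centre (for example 4 and 8), are recorded in a restricted document and are withheld from sites.
- Section 5: give each centre's total only and drop the split by arm.
- Sections 4.5 and 9.3.3: reconcile the two, so that sealed letters for unassigned numbers are held by existing site staff who neither enrol nor assess, and remain available for emergency opening.
- Section 4.4: state that staff who open or prepare kits take no part in enrolment.
- Section 4.5: require that consent and eligibility are recorded before the next number is taken.

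The cost is one setting in the randomisation program and a few sentences. A centre's final split may differ from exact 3:1 by a few subjects, with negligible loss of precision. No extra patients or staff are needed.
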